**Figure 2 figure2:**
[figure not shown]
Summary of outcomes in the trial. ASA24: Automated Self-administered 24-Hour Dietary Recall; FFQ: Food Frequency Questionnaire; SCFLDS: Self-Care Confidence in Following a Low-Sodium Diet Scale.

The second method for estimating the 24-hour urinary sodium excretion is with a spot urine sample using chloride and creatinine dipsticks. The dipstick method has been validated in patients with hypertension and correlates well with the 24-hour urinary sodium excretion (*r*=.86) [27]. The chloride dipstick is used as a surrogate for sodium excretion. The Quantab chloride dipstick (Hach, Loveland, CO, USA) is placed in a container filled less than halfway with urine. The chloride concentration is determined by observation of the change in color from brown to pale on the dipstick, which is the formation of silver chloride. The creatinine dipstick is similar to the chloride dipstick. The MultistixPro-10LS (Bayer, Elkhart, IN, USA) is a dipstick that includes a color pad for creatinine after it is placed in a container filled with urine. The color pad turns from yellow to green to indicate the creatinine concentration. The predicted 24-hour urinary sodium excretion is calculated on the basis of the 24-hour creatinine concentration calculated using sex, weight, race, and age. This model has been validated and correlates highly (*r*=.93) with 24-hour measurements of creatinine [28]. This measurement will be performed at baseline and after weeks 2, 4, 6, and 8.

The SCFLDS will be used to measure patients’ confidence in following a low-sodium diet. It assesses patients’ confidence in the ability to select and prepare low-sodium foods [29]. The tool consists of 7 items with 4 response options per item. The items ask patients to rate their level of confidence reading food labels, choosing low-sodium food during shopping, choosing low-sodium foods at restaurants, cooking low-sodium foods, choosing low-sodium foods at relatives or friends homes, estimating how much sodium they eat each day, and substituting low-sodium foods for high-sodium foods. The 4 response options are assigned a score of 1-4 (1=not confident; 2=somewhat confident; 3=very confident; 4=extremely confident) and then added for each question. Possible scores range from 7 to 28, and the higher score indicates greater confidence. The SCFLDS will be administered at baseline and after week 8 of the study.

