Mobile device analytics will be collected to determine the extent to which the mobile app was used. This outcome will be key in determining the frequency and intensity of the intervention. After a participant receives a push notification on entry to a grocery store and restaurant, we will provide them with a push notification on exit asking them if they chose any of our alternative options. We will also collect any scanned items to understand better the specific foods that participants are seeking more information about. Blood pressure will be monitored on a weekly basis by patients, and the results will be entered into the mobile app and graphically represented.

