### Statistical Approach

The primary endpoint this study is powered for is the estimated 24-hour urinary excretion of sodium from spot urine. Based on the data in patients with hypertension, we conservatively expect the 24-hour urinary excretion of sodium to decrease from 3400 (SD 1200) mg/24 hours to 2400 (SD 1200) mg/24 hours (35% reduction in sodium intake) in the mobile app group and a decrease from 3400 (SD 1200) mg/24 hours to 3300 (SD 1200) mg/24 hours in the usual care group [30]. The total sample size of 24 patients (12 in each group) and 32 patients (16 in each group) will provide 80% and 90% power, respectively, for a 35% reduction in sodium intake. In order to account for patients dropping out or incomplete follow-up, we are enrolling a total sample of 50 patients (25 in each group). We will use a two-sided *t* test to compare the change in each outcome over time in the mobile app group versus the usual care group. Other quantitative measures of sodium intake will be 24-hour urinary excretion of sodium and estimated 24-hour urinary excretion of sodium from chloride and creatinine dipsticks, which will be analyzed using a two-sided *t* test and repeated measures analysis of variance, respectively.

Although not powered to determine the impact, other measures of the effectiveness of this intervention will be summarized and evaluated. The percent change in confidence following a low-sodium diet will be analyzed using a two-sided *t* test. The change in blood pressure over time will be analyzed using repeated measures analysis of variance.

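### Repeated measures ANOVA is a poor fit for two secondary outcomes with planned incomplete follow-up, and it overlaps with a t test on the same outcomes

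*Protocol article*

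**What the plan says.** Three parts of the protocol article bear on this point.

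- **Method (Statistical Approach).** Two further urinary measures are paired with two methods in a sentence that ends "test and repeated measures analysis of variance, respectively". The dipstick estimate therefore takes the second method. For blood pressure: "The change in blood pressure over time will be analyzed using repeated measures analysis of variance". An earlier sentence in the same section applies a two-sided t test to the between-group comparison of change for every outcome.
- **Schedule (Outcomes).** For the dipstick: "This measurement will be performed at baseline and after weeks 2, 4, 6, and 8", which makes five time points. For blood pressure: "Blood pressure will be monitored on a weekly basis by patients, and the results will be entered into the mobile app". Over 8 weeks that is 8 values, or 9 with a baseline reading.
- **Attrition (Statistical Approach).** The stated need is: "The total sample size of 24 patients (12 in each group) and 32 patients (16 in each group) will provide 80% and 90% power". Enrolment is set higher: "In order to account for patients dropping out or incomplete follow-up, we are enrolling a total sample of 50 patients (25 in each group". No dropout rate is given.

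Both outcomes are listed as secondary in the abstract. The primary endpoint, spot-urine sodium, is measured only at baseline and after 8 weeks.

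**The concern.** Classical repeated measures ANOVA needs a full set of values from each patient. One missed week removes the patient, including every value that was recorded. The result is unbiased in general only if data are missing completely at random. The group-by-time test also relies on sphericity, which weekly readings seldom satisfy because neighbouring weeks are more alike than distant ones. A trial that over-enrols because it expects incomplete follow-up should not rest its longitudinal outcomes on a method that handles incomplete follow-up poorly.

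The second difficulty is what gets estimated. The Aim and Hypothesis section asks about change from baseline to the 8-week follow-up. An omnibus group-by-time test says whether the two profiles differ somewhere; it does not give the week-8 difference. The t test on change could give it, but the section does not say which of the two analyses counts for these outcomes.

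For blood pressure there is a further doubt. Readings are entered into the app, so in the app group a gap may mean that the patient stopped using the intervention. Missing completely at random is then hard to assume. The article describes no such link for the dipstick.

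**Working it through.** **The plan's own figures.** The margin in enrolment is 1 − 32/50 = 36% against the 90% power total and 1 − 24/50 = 52% against the 80% total. This is the loss the plan could absorb on its stated totals, not a forecast. The totals themselves do not follow from the printed inputs. With a difference of (3400 − 2400) − (3400 − 3300) = 900 mg, SD 1200 and two-sided 5% (assumed, since none is stated), n per group = 2(z₁ + z₂)²(SD/difference)² gives 28 for 80% power and 38 for 90%. The stated 12 and 16 per group need an SD of change near 755, that is, a baseline-to-follow-up correlation of about 0.80. That is a separate matter; here it only means that the 36% and 52% should be read loosely.

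**Complete cases, independent gaps.** The missingness rate m per value is an assumption. With k values per patient, complete cases = 50 × (1 − m)^k.

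| m | Dipstick, k = 5 | Blood pressure, k = 8 | Blood pressure, k = 9 |
|---|---|---|---|
| 2% | 45.2 | 42.5 | 41.7 |
| 5% | 38.7 | 33.2 | 31.5 |
| 10% | 29.5 | 21.5 | 19.4 |

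At 5% to 10%, about 39 to 30 patients remain for the dipstick and about 33 to 19 for blood pressure.

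**Complete cases, clustered gaps.** Independence spreads gaps over the most patients. At the other extreme, where the same patients miss everything, 10% missing per value leaves 50 × 0.90 = 45 for either outcome. The truth lies between.

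**Steady dropout.** Suppose loss D accrues evenly over the four post-baseline dipstick visits. Observed values = 50 × (5 − D × (0 + 1 + 2 + 3 + 4)/4) = 50 × (5 − 2.5D).

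- D = 36%: 205 values observed. The 32 completers hold 32 × 5 = 160, so 45/205 = 22% of recorded values are discarded. Patients with at least a week-2 value: 50 × (1 − 0.36/4) = 45.5.
- D = 52%: 185 values observed. The 24 completers hold 120, so 65/185 = 35% are discarded. Patients with at least a week-2 value: 50 × (1 − 0.52/4) = 43.5.

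The discarded shares are the same for nine weekly blood pressures. A mixed model would use the roughly 44 to 46 patients with a post-baseline dipstick value in place of 24 to 32.

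**The case against.** The strongest reply is that the article names a method and nothing more. It never says that incomplete patients are deleted. The term is also used loosely for mixed-model analyses that retain them, and covariance structure and missing-data rules are commonly left to a full protocol or analysis plan, which is not shown. This stands. A reader might infer that the trial will drop every patient with one missing value, but that is a property of the classical method, not a statement in the article.

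Four other inferences also go too far:

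- **That most longitudinal information would be lost.** Under independent gaps, fewer than half the patients remain only for blood pressure, and only at about 10% missing per week. The dipstick keeps 59% to 77% of patients at 10% to 5%.
- **That the app effect would be biased upward.** This is plausible for blood pressure if engaged users are the ones retained, but nothing in the article establishes the direction, and the mechanism does not reach the dipstick.
- **That the trial expects 36% to 52% dropout.** That range is headroom, not a stated expectation.
- **That the week-8 difference is never estimated.** The t test on change, read naturally, covers these two outcomes. What remains is that two analyses address one question without an order between them.

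It is also fair to say that these outcomes are secondary, that blood pressure is expressly not powered, and that the article calls the trial a pilot. This limits the weight of the point without answering it. The article's conclusions look ahead to assessing blood pressure at larger scale, and the Outcomes section explores simpler sodium measures for larger trials, so both results will be used.

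**Conclusion.** The point holds as a recommendation on two secondary outcomes. The named method, in its usual sense, sits badly with follow-up that the same section expects to be incomplete, and it does not deliver the week-8 comparison that the aim describes. On assumed independent missingness of 5% to 10% per value, an analysis of complete patients would rest on about 39 to 30 of 50 for the dipstick and about 33 to 19 for blood pressure. Clustered gaps would cost fewer patients. These sizes depend on a missingness rate that the article does not give and on the classical reading of the method. If a mixed model was meant, one sentence saying so would settle most of the matter. The primary analysis is untouched.

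**What to change.** For dipstick sodium and blood pressure, replace repeated measures ANOVA with a likelihood-based mixed model for repeated measures:

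- **Outcome:** post-baseline values, from all patients with at least one.
- **Fixed effects:** treatment, visit, treatment-by-visit, baseline value, and gender as the stratification factor. State which reading serves as the blood pressure baseline.
- **Covariance:** unstructured for the dipstick (four visits, 4 × 5/2 = 10 parameters). Use a simpler structure for blood pressure, such as AR(1) or a random intercept and slope, because eight weekly values would need 8 × 9/2 = 36 parameters with 25 patients per group.
- **Estimate:** the week-8 treatment contrast, declared as the single estimate in place of the overlapping t test for these two outcomes.

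The cost is slightly more programming and a covariance structure to choose in a small sample. It needs no extra patients, visits or data. The model is valid under missing at random. It does not cure dropout that depends on unrecorded values, and it cannot supply usual-care blood pressures if the app is the only route of entry. The article names no other route, so the collection route in that group should be confirmed.

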### Data Safety and Monitoring

A Data Safety and Monitoring Plan has been developed for this small intervention trial. Adverse events will be recorded from the day of the first study-related contact and reported to the Institutional Review Board. All participants who experience an adverse event will be referred for treatment. No formal stopping rule for harm has been established for this pilot study, as it evaluates standard-of-care treatment in a low-risk population.

## Results

The project was funded in 2016 and enrollment is expected to be complete in the Spring of 2019. The first results are expected to be submitted for publication in 2019.

## Discussion

The purpose of this randomized controlled trial is to test the efficacy of just-in-time contextual tailored messages using a mobile app for 8 weeks in patients with hypertension. This is a novel, first of a kind patient-centered decision support tool using geofencing technologies. We hypothesize that this intervention will improve sodium intake compared with the control group. By testing this novel approach, we could be developing a highly scalable mobile health model to help patients optimize their dietary habits in grocery stores and restaurants. If effective, the broader implications to other cardiovascular diseases and clinical outcomes should be explored.

## Abbreviations

ASA24: Automated Self-administered 24-Hour Dietary Recall
CKD: chronic kidney disease
IT: information technology
RR: relative risk
SBP: systolic blood pressure
SCFLDS: Self-care Confidence in Following a Low-sodium Diet Scale

## Appendix

Multimedia Appendix 1 Peer-review report from the Agency for Healthcare Research and Quality.
